##### Model Evaluation Test Set

The test set ***t***, disjointed from the set used in model building, will be used to evaluate and compare the performance of our final LR, XGBoost, and MLP models. As a randomly sampled subset of the development cohort, this test set will serve as an internal validation tool. Differences between test and training performance will also be reported, as this will be informative on the degree of overfitting to the training set [60].

The discriminative performance of each model will be reported using the AUC. AUCs will be reported with 95% CIs computed as the mean of 1000 bootstrap replicates ± 1.96 standard deviations. Since the AUCs will be derived from the same test set, we will also use DeLong’s method, a non-parametric approach to constructing CIs that accounts for implicit correlation between the underlying ROC curves [114].

Calibration will be investigated graphically using calibration curves. Calibration slopes and Brier scores will also be reported.

Additionally, F1 score, accuracy, precision, sensitivity, and specificity will be reported. Youden index, positive predictive value (PPV), negative predictive value (NPR), positive likelihood ratio (PLR), and negative likelihood ratio (NLR) will be supplementarily provided.

Coefficients and ORs will be tabulated for LR, and the hierarchy of predictor variables in descending order of gain will be provided for XGBoost. Individual decision trees within the XGBoost model will supplementarily be made available.

##### Further Evalution of Primary Analysis Models

We will also investigate the discrimination and calibration of the LR and XGBoost models on the non-AF cohort. This will fortify comparative exploration of performance by leveraging a large, related dataset that was heretofore unseen by the two primary analysis models. To clarify, the reason the MLP model is excluded from this step is because the non-AF cohort was implicated in its training.

##### Model Interpretation

Understanding why a model makes certain predictions is often as crucial as its overall performance [115]. To shed light on the internal logic behind our models’ predictions of 90-day recurrence, we will employ Shapley additive explanations (SHAP). SHAP is a model-agnostic framework to explain individual predictions and currently a dominant approach in interpretable ML (IML) [116]. In brief, SHAP values quantify feature importance by treating the prediction process as a cooperative game among the predictor variables. An attractive property of SHAP is that it provides both local explanations and insights into global model behaviour [117]. Specifically, the mean absolute SHAP value of a predictor variable serves as a heuristic for assessing its importance to the model’s global performance [115,118]. Furthermore, formal analysis of global feature importance is possible via SAGE (Shapley Additive Global Importance), a performance-based extension of SHAP [118].

The best explanation of a simple model is the model itself; however, using the original model as its own explanation is infeasible with models such as XGBoost and MLP due to the complexity of their internal informational architecture [115,119]. Although it is inherently interpretable, we will use SHAP and SAGE for LR too. This will ensure a consistent framework for reporting feature importance across models. Of note, the fact that LR is our baseline model is itself an ante hoc IML method [120].

##### Local Interpretation

For each model, we will select 20 predictions to individually explain. Of these, 10 will be randomly selected and 10 will be selected as cases of special interest (i.e., borderline and misclassified instances). Matched random seeds will be used for the former. For each prediction, the SHAP value of each feature will be reported. SHAP force plots will be provided to visually convey the contribution of each feature to the prediction. SHAP interaction values—calculated pairwise as the difference between the SHAP value for feature *i* when *j* is present, and the SHAP value for feature *i* when *j* is absent—will also be reported to quantify local interactions.

##### Global Interpretation

To summarise the average impact of each feature on our models’ outputs across the test set, we will calculate mean absolute SHAP values. The absolute mean will also be taken across SHAP interaction values. SHAP summary plots will be provided: bar plots to depict mean absolute SHAP values, and beeswarm plots to depict the distribution of local SHAP values in order to intuitively understand variability. We will also provide 8 × 8 beeswarm plots which depict interaction effects in the off-diagonal entries of the feature grid, 28 of which are unique owing to the symmetry of SHAP interaction values.

SAGE values will be reported with regard to the AUC and graphically represented using bar plots. Unlike SHAP, the SAGE algorithm readily provides the standard error of each feature’s importance. These will be utilised to gauge the stability of the importance estimates and facilitate their comparison.

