### 2.7. Sample Size and Power Analysis

Validating a CPR demands a moderate sample size relative to updating a CPR, which demands a large sample size [78]. Nonetheless, updating a CPR—meaning the predictors are known but not the functional form or model parameters—is still less data-demanding than development from scratch, where even the predictors are unknown. We employed the methods proposed by van Smeden et al. [81,82] and Riley et al. [83] to calculate the required sample sizes for our regression analyses. These methods were formulated to guide power analyses for studies intending to develop models from scratch. They have been encapsulated in a four-step procedure that represents a significant advancement over the historically inconsistent and poorly substantiated rules of thumb regarding the desirable number of events per variable (EPV) [84].

Each of the four steps in this procedure yielded a sample size estimate, with the largest selected as the required sample size. This approach ensured that our sample size was sufficient to accomplish the following goals: (1) estimate the overall 90-day recurrence prevalence with high precision, (2) minimise the mean absolute prediction error, (3) require minimal regularisation, and (4) limit optimism as measured by Nagelkerke’s R^2^. Steps 1, 3, and 4 were implemented using the psampsize package developed by the authors for R [84], while step 2 used the tool available at https://mvansmeden.shinyapps.io/BeyondEPV/ (accessed on 4 January 2024). The calculations—which are based on the estimated prevalence of 90-day recurrence in the target population, the number of predictor variables in our CPR, its anticipated discriminative performance, and the acceptable mean absolute prediction error, among other parameters—have been made explicit in the appending materials. We utilised 90-day recurrence rates within the 0.05–0.25 range, conservatively adopting the rate that produced the largest sample sizes.

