The sample sizes derived from steps 1, 2, 3, and 4 were 288, 344, 680, and 459 patients, respectively. We therefore deemed a minimum total sample size of 680 patients necessary for CPR development. Given that our sample size is 2763 patients and the fact that we will perform validation and updating (and not development from scratch), we contend that our regression analyses are adequately powered. Of note, 75% of our dataset (*n* = 2072 patients) will be used for regression model training and the remaining 25% (*n* = 691 patients) will be reserved for testing. The fact our test set alone exceeds the required 680 patients further supports our sample size.

ML and DL techniques are inherently more data-intensive than regression [85]. This is because the number of predictors they consider far exceeds that of regression, even when the same set of predictors is considered, because they examine multiple interaction terms [84]. Unfortunately, guidance for a priori sample size calculations is currently lacking for most ML/DL techniques [86]. However, if closely related data are readily available, it has been suggested that inspecting model learning curves in the related dataset can be valuable to estimate the required sample size for the main dataset [87,88]. We will therefore explore the observed power of our non-regression models by means of learning curves on our non-AF dataset, as well as via a key information theoretic metric: Kullback–Leibler (KL) divergence.

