##### Secondary Analysis

DL will be used to leverage the non-AF cohort data. A transfer learning strategy will be adopted: the MLP (a multilayered feed-forward neural network) will be pretrained on the non-AF dataset, and the best-performing pretrained model will be transferred to the AF dataset for fine-tuning. In other words, the model will initially learn from the larger dataset and then refine its parameters downstream on the target dataset, enhancing its predictive performance for the latter. This technique exploits the layer-wise modular architecture of neural networks, that is, the fact a network can be constructed by removing all layers after a particular layer and appending a new connected layer with a different configuration of neurons and initial weights. As a result, the MLP will have learnt from 10,572 AIS patients, all the while prioritising the 2763 with AF. Indeed, the pretraining paradigm has become dominant because it has enabled the use of neural networks in small datasets, where it would not be cautious to train models from scratch [108]. Generally, the more similarity between the datasets, the more benefits conferred by transfer learning, including higher asymptotic accuracy, enhanced generalisability, and accelerated convergence. We consider our situation well-suited to this technique: the features of CHA_2_DS_2_-VASc are known to increase risk of AIS in patients without AF [40,71] and CHA_2_DS_2_-VASc does not incorporate AF-related parameters that impact AIS risk, such as duration of AF and left atrium/left atrial appendage (LAA) size, function, and morphology [101]. It has even been reported that CHA_2_DS_2_-VASc may be equally discriminative in the absence of AF [40].

Of course, no preprocessing parameters or summary statistics will be carried over from the non-AF to AF datasets. Pretraining (including its internal validation) will use only non-AF data, and during AF model development, all preprocessing will be fit within AF training folds only, with the AF hold-out test set untouched until final evaluation.

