##### CPR Development

SHAP will be used to ‘translate’ model insights into CPRs. Mean—and not mean *absolute*—SHAP values will be used in order to preserve information on the directionality of feature importance. The decile rank of each of the eight mean SHAP values from each model will be calculated and a dot plot will be provided to visualise each feature’s mean SHAP value relative to others. (We speak of eight mean SHAP values because we have eight predictor variables corresponding to the features of CHA_2_DS_2_-VASc, namely five comorbid items, sex, and *two* age categories [65–74 years and ≥75 years]). The 25th, 50th, and 75th percentiles of the eight mean SHAP values will be computed. We will subsequently rank the features from most to least important and sort them into three tiers: (1) the lower tier grouping features with mean SHAP values below the 25th percentile, (2) the middle tier grouping features with mean SHAP values between the 25th and 75th percentiles, and (3) the upper tier grouping features with mean SHAP values above the 75th percentile. Features belonging to the lower, middle, and upper tiers will be assigned one, two, and three points, respectively. The purpose of a larger middle tier is to avoid over- or understating the importance of features by promoting stability over frequent changes with minor shifts in model parameters. In the rather unlikely event that one or more features will have negative mean SHAP values and local SHAP value distributions that are consistently left of zero on the beeswarm plots, zero points will be assigned, because their inclusion would degrade 90-day recurrence predictive performance. Ties at quantile cut-points will be resolved conservatively by assigning them to the higher category (e.g., features tied at the 75th percentile will enter the upper tier). The resulting CPRs will be summarised in tabular form and given an acronym in likeness to CHA_2_DS_2_-VASc.

If the dot plot suggests that the distribution of mean SHAP values is very skewed or concentrated, the above-defined tiers will probably inadequately capture features of lower, intermediate, and higher importance. In this eventuality, we will tailor tier boundaries using quantile-based binning. After adapting the tier setup to the observed clusters, we will define lower, middle, and upper tiers whose features will be assigned one, two, and three points, respectively.

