Each of the CPRs will subsequently be augmented by integrating interaction effects. This purports to better accommodate for the fact that a given feature may be more impactful in the presence of one of its counterparts. Mean (and not mean *absolute*) SHAP interaction values will be used in order to distinguish between synergistic and redundant interactions. The decile rank of each of the twenty-eight mean SHAP interaction values from each model will be calculated. A dot plot will be provided to visualise each feature-pair’s mean SHAP interaction value relative to other pairs. (We speak of twenty-eight mean SHAP interaction values because there are eight features, and (*i*, *j*)- and (*j*, *i*)-values capture the same interaction effect, while (*k*, *k*)-values capture main effects and were the object of the above paragraph). Dealing with a large number of feature-pairs, we will use stringent percentiles in selecting interaction effects for inclusion. The 90th percentile of the sample of twenty-eight mean SHAP interaction values will be computed. Feature-pairs with mean SHAP values above this threshold will be selected as the most important synergisms. Feature-pair selection will also incorporate domain knowledge, as some feature-pairs have well-established synergisms that may merit inclusion even if they fall somewhat short of the 90th percentile cutoff. Examples include CHF and age [121], hypertension and age [122], and hypertension and DM [123]. Selected feature-pairs will be integrated into the CPRs as accompanying rules: ‘if both feature *i* and *j* of the pair are present in the patient, add one additional point to the patient’s total score’. To mitigate overfitting, we will cap the number of points that can be added to accommodate synergisms to three. We will further cap the number of interaction pairs retained at a maximum of three. The augmented CPRs will be summarised in tabular form and their acronyms labelled with an asterisk (e.g., CHA_2_DS_2_-VASc*). A worked example of the CPR development process here described can be found in Appendix S6 in Supplementary Materials file S3.

Both non-augmented and augmented CPRs will undergo evaluation. See “CPR Evaluation”.

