##### CPR Evaluation

We will evaluate the CPRs on the test set ***t*** using discrimination, calibration, and clinical utility. The same methodology previously applied to CHA_2_DS_2_-VASc will be used to assess the discrimination and calibration of the newly developed CPRs. See Section 2.12.4. Clinical utility will be measured using net benefit (NB) via decision curve analysis (DCA). Although a CPR with better discrimination and calibration should, in theory, better guide clinical management, discrimination and calibration cannot determine whether a CPR aids decision making or which of several CPRs leads to better decisions. This is especially true when some CPRs have better discrimination and others better calibration. The shortcomings of conventional measures of performance are due to the fact that they do not incorporate information on consequences. DCA incorporates consequences by considering the tradeoffs between the benefits of true positives and the harms of false positives across a range of risk thresholds that reflect a spectrum of possible patient and clinician preferences [100]. It achieves this by calculating the NB for each risk threshold (*p**t*), which is defined as the number of true positives corrected for the number of false positives weighted by the odds of the risk threshold, all divided by the sample size (*N*) [124]. This is equivalent to the proportion of true positives in the absence of false positives (i.e., perfect specificity). To effectively use CPRs in clinical management, it is necessary to specify the risk thresholds at which intervention would be warranted. For early secondary prevention of AFAIS, oral anticoagulation is the treatment, and risk thresholds within 0.01—0.20 are reasonable. We will thus calculate the true positives and false positives for each CPR across the 0.01–0.20 risk threshold range and compute NB using the following formula:$$NB=\frac{\;\mathrm{True}\;\mathrm{positives}\;}{N}-\frac{\;\mathrm{False}\;\mathrm{positives}\;}{N}\left(\frac{p_{t}}{1-p_{t}}\right).\;$$

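### The hold-out set is clean for the prediction models but, as the steps are ordered, not for the CPRs that are then evaluated and ranked on it

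*Protocol article*

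**What the plan says.** All places are in the protocol article.

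- **Promise.** Section 2.12.5, Secondary Analysis, describes AF model development "with the AF hold-out test set untouched until final evaluation". The model-building text for LR and XGBoost likewise reserves t for final evaluation.
- **Use of t for the models.** Section 2.12.6, Model Evaluation, scores and compares the final LR, XGBoost and MLP models on t, with outcomes.
- **SHAP.** To summarise feature impact on the models' "outputs across the test set, we will calculate mean absolute SHAP values", Global Interpretation uses the test set, and it introduces the bar and beeswarm plots in the same paragraph.
- **Points.** CPR Development sets points from signed mean SHAP values, sorted into tiers at the 25th and 75th percentiles. A feature gets zero points if its mean is negative and its values lie left of zero on the beeswarm plots. If the dot plot looks lopsided or bunched, "we will tailor tier boundaries using quantile-based binning".
- **Interactions.** Pairs above the 90th percentile are selected. "Feature-pair selection will also incorporate domain knowledge", so a pair that narrowly misses the cutoff may still enter.
- **Use of t for the CPRs.** CPR Evaluation: "We will evaluate the CPRs on the test set" t. The CPRs are then ranked by net benefit against each other, CHA2DS2-VASc and the default strategies.

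**The concern.** A hold-out set gives an honest estimate only for something fixed before the set is examined. The models meet that condition. The CPRs appear not to: in the stated order they are built after t has been scored with outcomes, apparently from SHAP values computed on t, and are then judged on t.

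The CPR results on t carry the study's main comparison. CHA2DS2-VASc is fixed and cannot gain from choices made after t is seen; the new rules can. Any bias therefore runs one way. External validation is deferred to a later study, so t is the only AF data kept out of training on which the CPRs can be judged here.

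**Working it through.** **1. The plan's own figures.** Section 2.7 gives the cohort ("Given that our sample size is 2763 patients") and the split (75% "will be used for regression model training and the remaining 25"% for testing).

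- T: 0.75 × 2763 = 2072.25, stated 2072.
- t: 0.25 × 2763 = 690.75, stated 691.
- Pairs of eight features: 8 × 7 / 2 = 28, as stated.

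These reproduce.

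**2. Events.** Section 2.7: "We utilised 90-day recurrence rates within the 0.05–0.25 range".

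- In t: 691 × 0.05 = 34.6 to 691 × 0.25 = 172.8.
- In T: 2072 × 0.05 = 103.6 to 2072 × 0.25 = 518.

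**3. Tracing t through Section 2.12.6.**

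| Step | Set named | Outcomes used |
|---|---|---|
| Model Evaluation | t | yes |
| Local Interpretation (includes misclassified cases) | none | yes, to identify misclassified cases |
| Global Interpretation, SHAP | t | no |
| Global Interpretation, SAGE on AUC | not restated | yes |
| CPR Development, points and pairs | none | no |
| CPR Evaluation and ranking | t | yes |

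CPR Development names no set. However, t is the only set named for SHAP anywhere, and the zero-point rule reads the beeswarm plots, which are introduced only under Global Interpretation. That t supplies the points is therefore a strong inference, not a stated fact.

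**4. Does mechanical tiering on t create optimism?** A simulation was run with ridge LR, eight binary features, SHAP with T as reference set, and 400 runs per event rate. Feature prevalences and effects were assumed. Optimism is the AUC of the tiered score on t minus its AUC in 20,000 fresh patients.

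| Event rate | Optimism (simulation SE) |
|---|---|
| 5% | -0.005 (0.002) |
| 10% | 0.000 (0.002) |
| 25% | +0.001 (0.001) |

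There is no sign of optimism. In the same runs 49% to 50% of features changed tier between two random hold-outs of 691, so the patient mix of t can move the points. That share depends on the reference set: with T as reference, the signed mean for LR feature j is w_j × (mean of feature j in t − mean in T), which in a random split is chance variation.

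**5. Upper bound if choices followed t outcomes.** A second simulation used 300 test sets of 691. It took 3 tierings × 2³ = 8 subsets of the three interaction pairs the article names, giving 24 rules with true AUC 0.583 to 0.586. The best on t was compared with one rule fixed in advance.

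| Event rate | Best of 24 | Fixed rule | Difference |
|---|---|---|---|
| 5% | 0.021 | 0.005 | 0.016 |
| 15% | 0.011 | 0.001 | 0.010 |
| 25% | 0.008 | 0.000 | 0.008 |

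The fixed rule has no expected optimism, so its column shows simulation error.

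**6. Scale.** The Hanley-McNeil 95% half-width for an AUC of 0.585 with 691 patients is about 0.10 at 5% events and 0.05 at 25%.

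**The case against.** The strongest reply is that the promise about t is kept. It appears in text about model development, and the three models are final before t is used. This stands: there is no breach for the models, and the promise does not mention the CPRs.

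A reader might also infer more than the text supports:

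- **That the points are certainly built on t.** The test set is tied explicitly to mean absolute SHAP, whereas points use signed means with no set restated. The worked example in Appendix S6 is not shown and may name one. Only "appears" is justified. Even if it named T, t results would still precede the CPRs in the stated order.
- **That misclassified test patients are inspected before the CPRs are fixed.** Local Interpretation names no set.
- **That tiers or pairs are chosen to maximise performance on t.** Tailoring is triggered by the shape of the SHAP plot, and added pairs rest on cited literature, with pairs and extra points each capped at three. No section selects by AUC or net benefit at this stage.
- **That the bias is 0.02 AUC.** That figure belongs to a best-of-24 search the plan does not describe.

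Other safeguards count in part. The LR- and XGBoost-based CPRs are also checked on 7809 non-AF patients, but that is a different population and leaves out the MLP-based CPRs. A preregistered external validation is promised, but later.

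What remains is that the tailoring trigger has no numeric limit, the named pairs are only examples, and both choices come after labelled t results are available.

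**Conclusion.** The point holds in limited form. As ordered, t is a clean hold-out for the LR, XGBoost and MLP models but not for the CPRs. This rests on the stated sequence and on the inference that SHAP for the points comes from t.

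The likely bias is small and its size uncertain. It is about zero if the tiers are applied mechanically, and at most about 0.008 to 0.02 AUC for the 24-rule search, under assumed feature prevalences and effects. That is well inside the sampling error of a 691-patient test set, but it runs in favour of the new rules and could matter when six closely related CPRs (two per model, three models) are ranked. Optimism from picking the top-ranked CPR on t is separate: a best-of-six choice gave 0.008 to 0.014 in simulation and would remain after this fix. The change is worth making because it is cheap and removes the doubt.

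**What to change.** 1. State that the signed mean SHAP and SHAP interaction values used for points are computed from the final models on T.
2. Fix the tiers, any tailored boundaries and the interaction pairs on T, and record the frozen CPRs with a date before any t result is seen.
3. Open t once, to evaluate the final models and the frozen CPRs together.
4. Present SHAP, SAGE and case explanations on t afterwards, as description only.

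One technical caution: name the SHAP reference set. If T is both the explained and the reference set, the signed mean for every LR feature is w_j × (mean in T − mean in T) = 0, and no tiers can be formed. A different reference, such as a profile with every feature absent, avoids this.

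The cost is a reordering of steps and some wording from Model Evaluation to CPR Evaluation. No data are added, and the split stays at 2072 and 691. Reported CPR performance may be slightly less favourable.
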